### Sample size calculation and analysis

The sample size of this study is based on the expected difference on the primary outcome variable (depressive symptom severity), between the intervention group and the control group at T1 (three months). Based on a power of at least 0.80 in a two-tailed test and an alpha of 0.05, randomization of 200 subjects (100 per group) will be sufficient to show an effect-size of *d* = 0.50 (moderate effect), anticipating an attrition rate of maximally 20% at T1, a rate that has been achieved in several previous trials [29–32]. With an anticipated sample size of 160 (2 × 80) completers at T1, power of .88 would be achieved for a moderate effect size of *d* = 0.50. Based on previous research by this group [27–29, 32], the assumption of achieving a moderate effect appears realistic. This power calculation is based on the assumption that an even randomization procedure (50:50) will be used.

Analyses will conform to recommended methodological standards, as specified by the CONSORT statement [93]. Specifically, both intention-to-treat and per-protocol analyses will be conducted, using appropriate methods such as linear mixed-models, which are widely used in this field and have been recommended because of their capacity to handle missing data appropriately [94, 95]. It is anticipated that attrition rate at post-treatment will be below 20%, given previous trial experiences [29, 31, 32]. Additional analyses will be performed to examine the potential influence of confounding variables on changes in the primary outcome (e.g., initial differences in symptom severity or treatment utilization).

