The goal of this parallel-groups, pragmatic RCT is to evaluate the extent to which a novel Internet intervention, used adjunctively to CAU, can contribute to improving symptoms of depression and anxiety, social-occupational functioning, physical health (epilepsy symptoms), medication adherence, and health-related quality of life, among PwE. Furthermore, the trial aims to evaluate the extent to which patients with epilepsy regard this intervention as a helpful and valuable tool. The primary focus of the software-based intervention is on facilitating depression reduction; hence, this is the target identified in the primary hypothesis.

It is hypothesized that, between baseline and three months, patients randomized to the intervention group will report greater reductions in depression, as measured by the Patient Health Questionnaire (PHQ-9), a well validated depression measure [36, 37], compared to patients randomized to the control condition. The goal of this pragmatic RCT [38] is to test the effectiveness of a novel Internet intervention on depression reduction among PwE over a period of three months, in comparison to a CAU/waitlist (CAU/WL) control group, which only receives access to the intervention after three months. Data will also be collected at six and nine months, which will allow us to examine the stability of intervention effects over time.

Secondary measures are administered to examine effects of the intervention on anxiety symptoms, stress symptoms, and depression-related psychosocial impairment, and it is hypothesized that participants assigned to the intervention group will show greater improvements in these respective measures over three months, compared to control group participants. Exploratory analyses will be conducted to examine potential negative effects of the intervention, effects on epilepsy symptom severity and seizure frequency, health-related quality of life, epilepsy self-management, and medication adherence. The subjective usefulness of the intervention will also be examined, and we expect that users will rate the intervention favorably, given that it was developed to address several of their epilepsy-specific needs and concerns.

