**Fig. 1 Fig1:**
[figure not shown]
Flow diagram of the randomized controlled trial

Consistent with the logic governing pragmatic RCTs, the trial will examine whether utilizing this program will improve depression outcome above and beyond the routine care patients are actually receiving [38, 40, 41]. Furthermore, particular attention will be paid to potential negative effects of the program, as assessed by a questionnaire. The trial thus aims to maximize external validity by contrasting the realities of current clinical care with the addition of an Internet intervention; it does not aim to maximize internal validity by selecting a maximally homogeneous patient group or introducing many other artificial control measures, such as narrow inclusion and exclusion criteria that do not reflect the clinical reality outside of trials [40].

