### Recruitment and assessment

Participants will be recruited from various settings, including epilepsy treatment clinics, outpatient treatment centers, epilepsy support groups, Internet forums and groups, or Facebook pages. Methods such as newspaper articles, flyers, posters, and media articles or web-advertisements will be used to inform potential participants about the study (all material will be in German). Treatment centers are informed about the goals and procedures of the study; they were provided with information material (study flyers, posters or leaflets) that can be distributed to patients. This information material was scrutinized by the locally responsible ethics board prior to study commencement. Patients who are interested in participating are invited (in the printed study material) to sign up with their name and e-mail address at an online study website (https://de.research.net/r/epilepsie-studie). A member of the research team will then contact the potential participant by e-mail within one week in order to invite the person to the online baseline assessment (T0). Part of this online baseline assessment is to provide further information about the study as well as to provide informed consent to participate (the informed consent form in German is available on request from the first author). After completing the T0 online assessment and provided that informed consent is given, the research team associate will then conduct a telephone interview in order to check inclusion/exclusion criteria and confirm the diagnosis of a depressive disorder with a structured diagnostic interview (the MINI, as used in previous studies by this group [32, 42, 43]). After the telephone interview, patients will be randomized and will be asked to complete 3-months (T1, post-treatment), 6-months (T2), and 9-months (T3) online assessments (see Table 1). The T1 (post-treatment) assessment will permit us to examine whether treatment response can be documented after this relatively brief period, as has been shown in previous trials with a similar intervention [27–32]. The T1 assessment will be the time-point at which the intervention group but not the control group has used the intervention, thus permitting us to test the primary hypothesis that depression reduction will differ over three months between the intervention versus control groups.

**Table 1 Tab1:** Study measures and measurement points

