An outline of main content and program features is provided below. Each of five modules contains content that can be explored in briefer or longer individual sessions, depending on personal preferences. Depending on factors such as reading speed, interest to explore content in greater or lesser depth, and desire to listen to a greater or smaller number of audio recordings, each module can be completed in approximately 60 to 180 min. Thus, it would be possible to work through the entire program in as little as approximately five hours, or one could choose to spend much more time with it. As in other programs developed by our group [27–34, 48], there is no fixed or generic sequence in which modules must be completed, nor a minimum number of sessions that must be finished. Users are invited to freely explore the program and let themselves be guided within each section by the algorithm-driven sequences generated by the program. They are also informed that they can discontinue the program at any time if they feel that the program is not helpful or even harmful, and they are invited to contact the Principal Investigator, a licensed clinical psychologist, if they seek further help or advice. The purpose of such contacts would be only to provide information regarding treatment options, if clinically required, but not to provide therapeutic support. To define minimally sufficient usage, we are using the same algorithm we have used previously [32]: Having started at least four sessions and spent a total of least 60 min actively engaged with the program.

Program elements:
*Introductory module:* The introductory module provides an overview of the purpose, functions, and time-frame of the program. Patients are engaged in interactive sequences in which the CBT approach is briefly explained and in which their current and past medical and psychiatric history are explored. The introductory module addresses topics such as epilepsy onset and severity, types and intensity of current depression and anxiety symptoms, as well as exercise and nutrition habits. Patients are provided with a summary (“personal profile”) of their responses, and recommendations are made for further topics that patients may wish to engage with in subsequent sessions. The recommendation is made that patients use the program several times per week, as they see fit, for at least three months. They are informed that program access is provided for a six-month period.

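### A per-protocol analysis built on the protocol's only usage rule would select in one arm only; rest the primary conclusion on ITT at T1 and estimate the effect of use with a randomisation-based complier analysis

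*Protocol article*

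**What the plan says.** In the section on sample size and analysis, the protocol article commits to two analysis populations in one clause: "both intention-to-treat and per-protocol analyses will be conducted, using appropriate methods such as linear mixed-models". It gives no ranking and does not say how the per-protocol set is formed.

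The only rule about programme use is in the Intervention section. It sets the least use regarded as adequate: "Having started at least four sessions and spent a total of least 60 min actively engaged with the program". No time window is attached, although access lasts six months and the primary outcome is taken at three. The same section tells the reader that the programme has no fixed order of modules, "nor a minimum number of sessions that must be finished", and that "each module can be completed in approximately 60 to 180 min".

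On the control arm, the Background describes a group "which only receives access to the intervention after three months". The section on recruitment and assessment says the same of the primary time-point: "The T1 assessment will be the time-point at which the intervention group but not the control group has used the intervention". The Study design section gives the pragmatic aim: "the trial will examine whether utilizing this program will improve depression outcome above and beyond the routine care patients are actually receiving".

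**The concern.** A per-protocol analysis needs a criterion for adherence. The only one in the document concerns programme use, and up to T1 it has no counterpart among controls. Applied to the T1 comparison, it would remove low users from the intervention arm and nobody from the control arm. The groups would then differ by a choice made after randomisation.

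Such a choice may well be related to prognosis. The Intervention section tells users that they may stop if they find the programme unhelpful or harmful, so low use can itself be a sign of poor response. A linear mixed model does not repair this. It handles outcomes that are missing, whereas low users left out of a per-protocol set have been removed by rule.

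The practical risk is a near-null ITT result beside a favourable per-protocol result, with no sentence in the article saying which one answers the primary hypothesis.

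**Working it through.** **The plan's own figure.** Inputs from the sample size section: 200 randomised, at most 20% attrition, d = 0.50, and "Based on a power of at least 0.80 in a two-tailed test and an alpha of 0.05".

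- Completers: 200 × (1 − 0.20) = 160, or 80 per arm.
- SE of the difference in SD units: √(1/80 + 1/80) = 0.158.
- Power: Φ(0.50/0.158 − 1.96) = 0.885; the noncentral t gives 0.882. The stated 0.88 reproduces and is not in dispute.

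**Bias of users versus all controls.** Let a be the share of the intervention arm that meets the usage rule. Let g be the difference in untreated outcome, in SD, by which users would do better than non-users. The document gives neither value, so both are assumptions. With a true effect of zero:

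- bias = (1 − a) × g
- SE = √(1/(80a) + 1/80)
- two-sided type I error = Φ(−1.96 − bias/SE) + 1 − Φ(1.96 − bias/SE)

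| a | g (SD) | Bias (SD) | SE | Type I error |
|---|---|---|---|---|
| 0.80 | 0.2 | 0.04 | 0.168 | 0.057 |
| 0.70 | 0.3 | 0.09 | 0.174 | 0.081 |
| 0.60 | 0.5 | 0.20 | 0.183 | 0.195 |
| 0.50 | 0.5 | 0.25 | 0.194 | 0.252 |
| any | 0 | 0 | – | 0.050 |
| 0.70 | −0.2 | −0.06 | 0.174 | 0.064 |

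In the last row users have the worse prognosis and the bias runs against the programme.

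**A second parameterisation.** Suppose usage correlates ρ with the T1 outcome and the top fraction p meets the rule. Then bias = ρ × φ(z_p)/p:

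- p = 0.7, ρ = 0.3: 0.149 SD, type I error 13.7%
- p = 0.6, ρ = 0.3: 0.193 SD, 18.5%
- p = 0.8, ρ = 0.2: 0.070 SD, 7.0%

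Dividing each bias by (1 − p) gives the implied gap between users and non-users: 0.149/0.3 = 0.50, 0.193/0.4 = 0.48 and 0.070/0.2 = 0.35 SD. The first two are about as large as the trial's target effect, so they are strong assumptions.

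**The alternative under the same null.** Controls have no access before T1, so the complier-average effect is the ITT difference divided by the share of the intervention arm that used the programme. If the ITT difference is zero, it is zero whatever the prognosis of users. Its SE is about 0.158/a. At a = 0.70 that is 0.226, against 0.174 for the per-protocol contrast.

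**The case against.** The strongest reply is that the document does not say what a hostile reader might take from it.

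- A reader might infer that the two analyses stand on an equal footing or are co-primary. The text does not say so. ITT is named first, the primary hypothesis is worded by randomised group, the aim is pragmatic, and the sample size rests on the T1 group difference. This stands: the analyses are unranked, which is not the same as equal.
- A reader might infer that the per-protocol set is defined by the usage rule. No sentence links them. The set could rest on eligibility violations or T1 completion, which apply to both arms, and its definition may properly be left to an analysis plan that is not shown. This also stands, so the point is conditional. The condition is still the natural one: per-protocol is the one named analysis that plainly calls for an adherence rule, and this is the only such rule given.
- A reader might infer that the bias must favour the programme. The table shows that it vanishes at g = 0 and reverses at negative g.
- The usage rule is lenient. Sixty minutes is the fastest time for one of five modules, which together take 5 × 60 = 300 to 5 × 180 = 900 minutes. A lenient rule excludes fewer people and shrinks the bias. This is fair, and carrying the rule over from an earlier trial is no defect.
- Nothing says that use after T1 would classify participants for a T1 analysis. Agreed; the window is merely not stated.

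None of these replies makes a usage-based set a randomised comparison.

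**Conclusion.** The point holds in a limited, conditional form. The article plans two populations without ranking them, and its only usage standard can select in one arm only before T1. A per-protocol set built on that standard would not keep the protection of randomisation, and the mixed model would not restore it.

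The direction is probably in the programme's favour but not certain. The size cannot be derived from the document. The range of about 0.04 to 0.25 SD, with type I error of about 6% to 25%, rests on assumed usage of 50% to 80% and an assumed prognostic gap of 0.2 to 0.5 SD, under a true null with 80 completers per arm.

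The documents do not support calling the per-protocol analysis an error in itself, or saying that it threatens the ITT estimate. No sample-size figure changes. What justifies raising the point is that a better estimator of the effect of use exists and needs only data that the trial already collects.

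**What to change.** 1. State that the primary conclusion rests on ITT at T1, and label any per-protocol result supportive.
2. Estimate the effect of use as a complier-average causal effect with randomisation as the instrument, for example by two-stage least squares adjusted for baseline PHQ-9.
3. Take use from the programme's automatic log, counting only activity before T1.
4. Make any log-in the main definition of use, because the exclusion restriction (allocation affects outcome only through use) is most credible there. Use the four-session, 60-minute rule as a sensitivity analysis; under it, one must assume that use below the rule has no effect.

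The cost is a few sentences and a few lines of code, since usage is already tracked. The interval will be wider than a per-protocol interval, for example an SE of 0.226 against 0.174 SD at 70% users. The estimate also relies on the exclusion restriction, which remains an assumption even for any log-in because participants know their allocation.

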### Conflict of interest, scientific integrity and independence

It is not unusual for intervention developers to be involved in trials that examine their efficacy; indeed, this is the rule rather than the exception and will also be the case in this study. However, measures will be taken to ensure that potential conflicts of interests do not jeopardize the scientific integrity of data collection, analysis, or any other aspect of the study. Firstly, the Principal Investigator (YN) is an independent established researcher in the field of clinical psychology and psychotherapy without financial or other ties to the developers, operators, and sponsors of this project (i.e., YN does not receive remuneration or other compensation from Gaia, the developers). Secondly, the Principal Investigator and members of her research team will have full and continuous access to all data being collected in this study (provided, of course, that informed consent to this is granted by participants at study commencement). Data monitoring will be performed by the Principal Investigator, who is independent from the sponsor and has no competing interests. All adverse events will be reported; interim analyses are not planned. The day-to-day management of the study (e.g., contacting participants and inviting them to complete online surveys) will be performed by research associates working at Gaia, the intervention developer, which is an e-Health enterprise with an established track record of multicenter research [28, 32, 42, 96]. Publication of results will be sought regardless of study outcome, i.e., even if the intervention should prove to be ineffective. A summary of the results will also be made available for trial participants after completion of the trial.

## Discussion

This protocol describes a methodological rigorous, statistically adequately powered trial of a novel Internet-based psychological treatment for depression and anxiety among PwE. There is an urgent need for innovate and low-threshold interventions in this area, given that depression and anxiety are exceedingly common in epilepsy, complicate treatment response and prognosis, dramatically reduce quality of life, and yet often remain undetected and are treated inadequately. The personal suffering and societal burden associated with depression among PwE could potentially be reduced by Internet-based interventions such as the one evaluated in this trial.

Although the allegedly low costs of Internet-based interventions are often emphasized, developing and maintaining effective, technologically adequate and secure Internet interventions incurs considerable expenses. In this project, a research-focused e-Health company is driving the development of a novel Internet intervention and investing considerable resources to enable the conduct of a methodologically rigorous, independent scientific investigation, whose results will be published regardless of whether they are consistent with the research hypothesis, and the hopes or expectations of the program developers. Several collaborating investigators with no conflicts of interest will ensure the scientific integrity and independence of this project. In our view, this type of collaborative arrangement seems ethically responsible and scientifically viable. Along with others [19, 97, 98], we feel confident that evidence-based Internet interventions will increasingly be regarded as legitimate, valuable additions to the armamentarium of professional medical care, particularly if their value can be demonstrated repeatedly in rigorously designed trials.

First and foremost, this trial seeks to make a scientific contribution to the field of depression and anxiety treatment among PwE. This will be the first trial in which an Internet-based intervention is evaluated that has been designed specifically to address the unique needs of PwE. It is also one of the few such trials in which diagnoses are established by a structured, validated interview. Several additional methodological strengths are noteworthy, including follow-up assessments and the inclusion of an array of validated measures for the primary outcome of depression and secondary outcomes such as anxiety, quality of life, epilepsy disease status, and potential negative effects of treatment, which are highly relevant for the quality and safety management of novel Internet interventions. As in most studies, these strengths are balanced by some methodological limitations, including the lack of clinician outcome-ratings, laboratory tests, or brain imaging measures. Studies utilizing such methods are desirable but costly, and it is hoped that future investigations, including health-economic studies, will further explore the effects and utility of the novel, Internet-based intervention described and tested in this trial.

### Trial status

Recruitment is ongoing. It is anticipated that the trial will be completed (T3) by October 2017.

## Abbreviations

CAU: Care-as-usual
CBT: Cognitive behavioral therapy
DASS-21: Depression and Anxiety Scales
ESMS: Epilepsy Self-Management Scale
GAD-7: Generalized Anxiety Disorder questionnaire, 7 items
INEP: Inventory for the Assessment of Negative Effects of Psychotherapy
PHQ-9: Patient health questionnaire, 9 items
PwE: Persons with epilepsy
RCT: Randomized controlled trial
WSAS: Work and social adjustment scale
